### Clinical data collection and patient treatments

The baseline clinical survey of all study children will take place in May/June 2016 and will determine malaria infection, splenomegaly, and anemia. Clinical follow-up will start in June 2016, and cover both rainy seasons (June to December 2016 and 2017). Incidence of clinical malaria will be determined by ACD during twice weekly house visits from June to November each year [20]. Clinical respiratory disease will be determined at the same time. Clinical surveys of all study children will be repeated at the end of each rainy season (November/December) and during June 2017. Surveys to measure damage to the interventions and the integrity of the control houses will be carried out annually. Surveys to measure LLIN use by all study house residents will be made in July and October each year. The final clinical survey of the child cohort will take place in December 2017.

No treatment will be administered by the study personnel. However, any patient diagnosed with malaria or suspected to have pneumonia or other illnesses will be referred to the local health system for treatment according to the Gambian National Guidelines.

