### Clinical evaluations

The main morbidity outcome will be the incidence of clinical disease assessed by ACD; data from this will provide the primary endpoint of the study. The axillary temperature will be taken twice weekly and if ≥ 37.5 °C, a rapid diagnostic test (Paracheck Pf, Orchid Biomedical Systems, Goa, India) for malaria will be made, and the breathing rate will be checked. The presence of a cough and either a raised age-specific respiratory rate or chest indrawing will also be assessed in children deemed to be unwell by the parent or guardian. Serious adverse events (SAE) will be recorded during both transmission seasons. Sick children will receive referral notes to the nearest health post/facility, and treatment will be documented at the next biweekly visit.

During the cross-sectional surveys, clinical surveys will be done of all study children, who will be examined for general health and the presence of an enlarged spleen. A finger prick sample will be taken to measure the blood hemoglobin immediately using a spectrophotometer (HemoCue, Ängelholm, Sweden) and to prepare thick smears for later detection and quantification of *Plasmodium* parasites. Blood films will be stained in the field by project staff, transported to the laboratory, and read independently by two microscopists blinded to the identity of the child. Any discrepancy will be resolved by a third senior microscopist. Children with sickness or disease will be referred for treatment.

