### Safety considerations

No potential pharmacological intervention or treatment by project staff is proposed in this study. However, the possibility remains that our modified housing may increase the risk of acute respiratory infections. We will therefore assess the study children for respiratory disease at each study visit, i.e., twice weekly during the transmission season. Since respiratory infections are common in children in this area [25], we selected this age group as the most sensitive indicator group. Adverse events, whether attributed or not to improved housing, will be collected. If a participant develops a SAE during the course of the study, this will be reported by the field staff to the study clinician within 2 days of the start of the SAE. A SAE is defined as any adverse event that results in death, is life threatening, requires hospitalization or prolongation of existing hospitalization, or results in disability/incapacity. The study clinician will record and manage the SAE in accordance with the MRC Unit standard procedures (SOP-CTS-009 for “Recording, Management and Reporting of Adverse Events”). The study clinician will report the SAEs to the Chief Investigator, who will report these regularly to the Data Safety and Monitoring Committee and Study Steering Committee (SSC; see supplementary material for roles and responsibilities). All SAEs will be followed up until resolution.

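### The protocol gives two different periods for recording serious adverse events, and counts the 2-day reporting limit from onset, which the visit schedule alone cannot guarantee

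*Protocol article*

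**What the plan says.** All references are to the protocol article.

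- **Recording period.** Clinical evaluations: "Serious adverse events (SAE) will be recorded during both transmission seasons". Design and Clinical data collection both put the seasons at June to December, in 2016 and 2017.
- **Reporting period.** Safety considerations: "If a participant develops a SAE during the course of the study, this will be reported by the field staff to the study clinician". Design gives the clinical study a length of two years.
- **Scope.** Clinical evaluations names serious events. Safety considerations adds: "Adverse events, whether attributed or not to improved housing, will be collected". No season is attached.
- **Deadline.** Safety considerations sets it at "within 2 days of the start of the SAE".
- **Contact with the children.** Clinical data collection provides "twice weekly house visits from June to November each year", plus surveys of all study children at the end of each rainy season (November/December) and in June 2017, the last being in December 2017. Safety considerations places the respiratory assessment "at each study visit, i.e., twice weekly during the transmission season".
- **Procedure.** Recording, management and reporting of SAEs follow a named unit standard procedure, which is not shown.

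**The concern.** The protocol itself raises the possible harm: a closed and screened house may have less airflow and so more respiratory disease. Exposure to the modified house does not stop when the rains do, because children stay in these houses between the two seasons.

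If field staff work from Clinical evaluations, a child who dies or is admitted between the seasons need not enter the safety record. If they work from Safety considerations, the same event must be reported. The monitoring committee sees what passes up from field staff through the study clinician and the chief investigator, so the choice of section decides what it can compare between arms. The gap is easily hidden, because Design allows a child who leaves the house for any reason to be replaced by another child from the same house.

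The deadline raises a second, smaller matter. A clock that starts at onset depends on how staff learn of the event, and the article describes no route other than scheduled contacts.

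**Working it through.** The plan gives no figure of its own here, so the check is a calendar count and a comparison of the sections.

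**1. Calendar.** Inputs: clinical follow-up starts in June 2016 and the final survey is in December 2017 (Clinical data collection); the season is June to December (Design, Clinical data collection).

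- Whole span: 7 months in 2016 + 12 months in 2017 = 19 months.
- In season: 7 + 7 = 14 months.
- Outside the season: 19 − 14 = 5 months (January to May 2017), and 5/19 = 26%.

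December lies within the season but after the months of twice-weekly visits. It is not counted as a gap here, because the end-of-season surveys fall in November/December and the final survey is in December 2017.

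**2. An SAE in March 2017 under each section.**

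| Section | Stated period | Is the event covered? |
|---|---|---|
| Clinical evaluations | The two transmission seasons | Outside the stated period |
| Safety considerations | The course of the study | Reportable |

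For non-serious events, Clinical evaluations is silent and Safety considerations promises collection. That is a difference in scope to be aligned, not a contradiction.

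**3. Deadline against visits.** Two visits a week leave two gaps that sum to 7 days, so the longer gap is at least 7/2 = 3.5 days, which exceeds 2 days. However the visits are spaced, some onsets will therefore precede the next visit by more than 2 days. Between the seasons there are no such visits.

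This shows only that visits alone cannot guarantee the deadline. The share of events that would miss it cannot be derived, because the article gives neither the spacing of visits nor the routes by which staff hear of an event.

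**4. Recall interval.** From the end-of-season survey in November/December 2016 to the survey in June 2017 is 6 to 7 months.

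**The case against.** The strongest reply is that the sections can be read together. Clinical evaluations does not say that recording is confined to the seasons. Design describes clinical follow-up as two seasons, so the course of the study could mean just those seasons, and then the two sections agree. This stands as a possible reading, but the text does not settle on it, since Design also gives the clinical study a length of two years. And if it is the intended reading, events between the seasons are not covered by either section.

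A reader might infer that the protocol excludes dry-season SAEs outright. The documents do not support that: the restriction is implied by naming the seasons, and Safety considerations points the other way.

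A reader might also infer that the 2-day limit cannot be met or would be missed routinely. That is not supported either. Nothing says scheduled visits are the sole means of detection. Households or health facilities may notify staff between visits, and the standard procedure that may provide for this is not shown. It could resolve the timing question. It cannot make two differently stated recording periods both correct.

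Finally, respiratory infection has its own secondary endpoint, assessed in both arms at the twice-weekly visits. That is true and limits the consequence, but the assessment is also seasonal and does not replace a count of deaths and admissions between the seasons.

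**Conclusion.** The point holds as an inconsistency in the stated SAE period. Read literally, deaths and admissions in 5 of 19 months (26%) fall under Safety considerations but outside Clinical evaluations. The 26% is a share of calendar time; the documents give no basis for the share of events it would represent. It rests on taking the season as June to December and child follow-up as June 2016 to December 2017, both as stated.

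On timing, the conclusion is narrower: a limit counted from onset is not guaranteed by the visit schedule alone, and no miss rate should be attached to it.

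What is affected is the completeness of the safety comparison, mainly between the seasons. The primary endpoint, its analysis and the sample size are untouched. The change is worth making because it is cheap and the intervention acts all year.

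**What to change.** 1. Reconcile Clinical data collection, Clinical evaluations and Safety considerations on one SAE period that covers the whole of child follow-up, including the months between the seasons. State in the same place over what period non-serious adverse events are collected.
2. At the June 2017 and December 2017 surveys already planned, ask each household about deaths and hospital admissions, with cause, since the last contact. Include children who left or were replaced.
3. Reconcile the 2-day limit with the visit schedule by stating whether it runs from onset or from the day staff become aware of the event. If notification between visits is provided for elsewhere, cite it here.

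**Cost.** Protocol wording and one question on existing survey forms, with no added visits and no change to the sample. Between-season events would rest on recall over about 6 months, which is tolerable for deaths and admissions but would not serve for minor illness. Households that withdraw consent are not followed further, so the question would not reach them, and their number should be reported by arm.

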### Entomological evaluations

Indoor mosquito collections made using Centers for Disease Control (CDC) light traps will be used to estimate the potential exposure to malaria vectors and will be carried out once a month for 6 months from June to December in 2016 and 2017 in the bedrooms of the study children. Mosquitoes will be identified by microscopy, and the numbers of *An. gambiae* s.l. and other species, recorded. The presence of sporozoites in *An. gambiae* s.l. will be identified using an enzyme-linked immunosorbent assay [22], and *An. gambiae* s.l. females, typed to species by PCR [23].

### Economic and social science evaluations

Data on incremental costs of house improvements and their sources will be collected alongside the interventions. Incremental benefits due to malaria cases averted will be estimated based on malaria treatment cost data collected from selected health facilities. The acceptability of the intervention will be captured during the trial using (1) observations and informal conversations during the house modification process, (2) photo-voice (a participatory action research technique enabling people to record and reflect on their concerns, promote critical dialogue, and reach policy makers) [24], and (3) focus group discussions. These activities and their outputs will contribute to the process of stakeholder engagement and will be used to develop an end-of-trial acceptability questionnaire survey. To design potential strategies for scale-up, we will identify and engage with key local, national, and international level stakeholders, involving them in discussions and decisions on the appropriate innovation design and consideration of the implications of the results and creating a driving team to identify mechanisms for expansion and institutionalization while acting as advocates for the innovation.

### Safety considerations

No potential pharmacological intervention or treatment by project staff is proposed in this study. However, the possibility remains that our modified housing may increase the risk of acute respiratory infections. We will therefore assess the study children for respiratory disease at each study visit, i.e., twice weekly during the transmission season. Since respiratory infections are common in children in this area [25], we selected this age group as the most sensitive indicator group. Adverse events, whether attributed or not to improved housing, will be collected. If a participant develops a SAE during the course of the study, this will be reported by the field staff to the study clinician within 2 days of the start of the SAE. A SAE is defined as any adverse event that results in death, is life threatening, requires hospitalization or prolongation of existing hospitalization, or results in disability/incapacity. The study clinician will record and manage the SAE in accordance with the MRC Unit standard procedures (SOP-CTS-009 for “Recording, Management and Reporting of Adverse Events”). The study clinician will report the SAEs to the Chief Investigator, who will report these regularly to the Data Safety and Monitoring Committee and Study Steering Committee (SSC; see supplementary material for roles and responsibilities). All SAEs will be followed up until resolution.

### Handling of drop-outs/withdrawals

Participants are free to withdraw from the study at any time without giving a reason. In the unlikely event that homeowners require their house to be returned to the pre-intervention state, we will remove the items we have added and replace the metal roof with a thatched one. Withdrawals may also occur if a study subject has any clinically significant AE, laboratory abnormality, intercurrent illness, or other medical condition or situation that occurs such that continued participation in the study would not be in the best interest of the participant. No replacements will be made during the surveillance period in either year, but in May 2016, children who have withdrawn or are no longer in the study for any reason will be replaced by a child of a similar age from the same house. If a household withdraws consent, no further follow up will be made in that household. If the house was participating in the entomology collections, it will be replaced by a neighboring house of the same type, if possible.

### Study endpoints

#### Clinical

The primary clinical endpoint will be the incidence of clinical malaria, which is determined by active case detection (ACD) and defined as a body (axillary) temperature of ≥ 37.5 °C, together with the presence of *P. falciparum* parasites detected by microscopy.

The secondary clinical endpoints will be (1) *P. falciparum* parasite rates, (2) prevalence of splenomegaly, (3) prevalence of anemia, and (4) an incidence of respiratory infection, measured as a cough and either a raised age-specific respiratory rate or chest indrawing.

#### Entomological

The primary entomological endpoint will be the mean number of female *An. gambiae* s.l./light trap/night.

The secondary entomological endpoint will be the estimated entomological inoculation rate (EIR) in each study arm (i.e., the mean number of sporozoite infective bites/child/season).

#### Economic and social sciences

The primary economic and social sciences endpoints will be the mean and median costs of house improvement interventions/house improved and the mean and median costs of treating one case of childhood malaria.

The secondary economic and social sciences endpoints will be the percentage of home owners who agreed to house modifications in the intervention arm, key observations and discussions on house modifications with villagers and builders in the trial, trends in the types and quantities of housing materials imported/exported, the construction skills developed during at least the previous 5 years in the country, and a road map for scaling up of the housing modifications.

### Sample size rationale

#### Clinical

The combination of closed eaves and screening on the door reduces house entry of malaria mosquitoes by 65 % [26], and we anticipate a similar proportional reduction in malaria incidence in the proposed study but consider that a reduction of at least 35 % would not only be of public health importance but also good value for the money. We simulated incidence data allowing for within-house correlation between the years, based on incidence data collected using passive case detection from the proposed study area in 2010 (0.0468 and 0.0442 malaria episodes per child month at risk, CMAR) and 2011 (0.0321 and 0.0341 CMAR). The number of cases were inflated twofold, as we will use active case detection (ACD). Correlated event data were generated from a bivariate Poisson distribution to give random simulated correlated counts for each house over the two years. Each village was assumed to contain an equal number of houses in the control and intervention arm. Fifty sets of 1,000 data points were simulated for each of the two to ten houses in the 40 to 100 villages. The significance of the difference in incidence rate between the control and the intervention arms was quantified using a generalized estimating equation (allowing for the within-house correlation) with a log link for each of the data sets and house and village parameters. The proportion of each set of 1,000 simulations with a significant *p* value of less than 5 % for the difference between the control and the intervention arm was the estimated power. This shows that when following one child per house for 2 years, five houses in 80 villages are required in each study arm (black circle, i.e., 400/arm) to detect a 35 % reduction in malaria cases with more than 80 % power at the 5 % significance level (Fig. 3).

**Fig. 3 Fig3:**
[figure not shown]
Sample size calculations

#### Entomological

We postulate that metal-roofed houses, closed eaves, and screening on the doors will reduce indoor collections of malaria vectors by at least 50 %. Based on a study using light traps in the proposed study area in 2011, we expect that the mean number of female *An. gambiae* s.l. per trap will be 2.11 (SD = 1.80). In order to demonstrate a 50 % reduction in indoor-entering mosquitoes (i.e., unfed *An. gambiae*) associated with housing interventions, with 80 % power at the 5 % level of significance, we would require 47 houses in each arm of the study respectively. Since the number of mosquitoes rise and fall during the rainy season, we propose to sample from each house six times each year. To allow for loss to follow-up during the study period, we propose to conduct entomological monitoring in 60 houses in each arm of the study each year.

### Data handling and record keeping

The demographic data will be recorded by fieldworkers, and the clinical data by study nurses on standardized data forms. Each child in the cohort will be identified by a unique identification number. All forms and datasets will identify participants by these numbers, and names will not be entered. The study will follow the MRC Unit The Gambia’s specific policy to maintain anonymity of study participants. Personal identifiers will be removed from the transcripts of interviews, and discussions with participants will be identified only through a study identification number. Transcribe and translated transcripts will be entered into NVivo for management and analysis. Participants in the photo-voice exercise will be specifically requested and trained not to take photographs containing images of identifiable people, and any photographs containing such images will not be entered into the NVivo database. Thus all data will be anonymized at data entry, including those participating in the subsidiary studies (economic and perceptions of the housing intervention). Databases will be password protected and accessible only to authorized personnel. All documents will be securely stored in locked filing cabinets and accessible only to authorized personnel.

### Source documents and access to source data

The PI will maintain appropriate medical and research records for this study in compliance with the principles of good clinical practice and regulatory and institutional requirements for the protection of confidentiality of participants. The study team members will have access to records. The authorized representatives of the sponsor, the ethics committee(s), or regulatory bodies may inspect all documents and records required to be maintained by the investigator, including but not limited to medical records (office, clinic, or hospital) for the participants in this study. The clinical study site will permit access to such records. The results of the study will be made publicly available. Blood slides and mosquito DNA will be stored and made available for future studies.

### Analytical plan

A per-protocol and an intention-to-treat analysis will be conducted.

***Outcome 1—malaria morbidity*****.** Protective efficacy against clinical malaria will be determined by comparing incidence rates of clinical malaria between arms. After any treatment for malaria, the child will not be considered at risk for 4 weeks, and this period will be censored. History of travel away from the household will be captured by twice-weekly surveys during the malaria season, and the time at risk will be censored for such periods. An initial unadjusted analysis will be based on comparisons of the incidence rates between the two arms. Formal analysis will use a mixed effects Poisson (or negative binomial) model to test the difference in incidence rate between the two arms, allowing for the repeated measurements within house and within village and the effect of year. With multiple control and intervention houses within each village, the intervention * village interaction can also be quantified. Possible confounders such as age of child, gender, ethnicity, and rainfall will be tested using the mixed effects model.

A comparison of the time to the first episode of clinical malaria and repeat episodes of clinical malaria will be examined using a survival analysis approach. Initial analyses will be based on Kaplan-Meier curves with further adjustment for confounders performed using a Cox regression model.

***Outcome 2—malaria transmission.*** Differences in malaria transmission experienced in the two groups will be made by comparing the mean number of mosquitoes (as a proxy for transmission) caught indoors in houses between the intervention groups. Generalized estimating equations will be used to estimate differences in the numbers of indoor-resting mosquitoes, adjusting for repeated measures within houses and possible covariates.

***Outcome 3—incremental cost-effectiveness ratio.*** The incremental cost-effectiveness ratio of averting a clinical case of malaria by home improvement interventions will be calculated through probabilistic decision tree analysis. The health impact will be also expressed in terms of disability-adjusted life years.

***Outcome 4—housing market supply.*** Data on the types and quantities of construction material produced and imported during at least the previous 5 years, as well as of construction skills developed within the country, will be analyzed against the resources used within the trial. Time-trend analysis will be also performed to generate future predictions of the quantities potentially available in the next few years, while controlling for confounding factors.

